# AIDS fighter health defense: protocol for a randomized controlled trial to test a game-based intervention to improve adolescents’ AIDS prevention ability

**DOI:** 10.1186/s12879-021-06161-0

**Published:** 2021-05-22

**Keywords:** Adolescents, AIDS prevention ability, Game-based intervention, Information-motivation-behavioral skills model

## Abstract

**Background:**

Although great progress has been made in the prevention and treatment of AIDS, there are still a considerable number of new infections annually, especially in adolescents. With the advance of technology, game-based education has gradually become an important tool for changing healthy behaviors among youth.

**Methods:**

A protocol for conducting a randomized controlled trial to evaluate the “AIDS Fighter · Health Defense”, a game-based AIDS education project aimed at improving the ability of adolescents to prevent AIDS. During the four-week intervention, participants will receive: 1) A virus combat game; 2) Goal setting to eliminate HIV; 3) Questions to be answered to be resurrected in the game; 4) Points ranking; 5) Recognition and Rewards. The primary outcomes include changes in participants’ knowledge, stigma attitude, and risk behaviors attitude related to AIDS after four weeks of intervention. The secondary outcomes are the participants’ AIDS-related risk behaviors three and six months after the intervention.

**Discussion:**

AIDS Fighter· Health Defense may be an innovative approach to help adolescents improve AIDS prevention capabilities, fill the gap in game-based AIDS prevention education in China, and gain experience of AIDS management.

**Trial registration:**

Chinese Clinical Trial Registry: ChiCTR2000040195. Registered 25 November 2020.

## Background

Acquired Immunodeficiency Syndrome (AIDS) is a global disease that seriously threatens human health [1]. By the end of 2019, 38 million people worldwide are living with human immunodeficiency virus (HIV) [2]. At the end of October 2019, China reported 958,000 survivors of HIV infection [3], and the number of newly diagnosed HIV infection cases among adolescents aged 15–24 each year is approximately 3000 in recent years [4],which implies that the situation of AIDS prevention is still grim.

Developing countries, represented by China, have problems in AIDS prevention education, such as outdated education model, poor effect of education, and uneven distribution of educational resources [5, 6]. Therefore, it is necessary to develop innovative AIDS education. With the development of science and technology, AIDS prevention education has changed from traditional methods to modern methods. Among them, game-based intervention has become a significant way to change healthy behaviors [7–9]. In recent years, some randomized controlled trials conducted in the United States and Africa targeting 11–15 years old adolescents have found that game-based AIDS education could improve knowledge, attitudes and behaviors related to AIDS, and increase the effectiveness of AIDS prevention education, additionally, adolescents prefer game-based AIDS education, and are more willing to recommend it to their friends [10–13]. However, there are few games-based HIV education intervention studies in China, especially randomized controlled trials to evaluate the effects of game education.

Below we describe the protocol of our randomized controlled trial to evaluate a game-based intervention to improve adolescents’ AIDS prevention ability in China. The intervention, called AIDS Fighter · Health Defense, is a 4-week game experience, and includes components designed to increase AIDS-related knowledge, improve AIDS prevention motivation, and strengthen AIDS prevention behaviors among adolescents. This study is guided by the Information-Motivation-Behavioral Skills Model (IMB Skills Model), which believes that the prevention of AIDS requires comprehensive intervention from three aspects: AIDS-related information, motivation, and behavior skills [14]. In the AIDS Fighter · Health Defense intervention, adolescents will actively or passively receive AIDS prevention information, repeatedly train AIDS prevention skills, and strengthen the motivation to prevent AIDS. The combination of this study and theory is shown in Table 1.

**Table 1 Tab1:** The combination of AIDS Fighter · Health Defense and IMB Skills Model

IMB Skills Model	AIDS Fighter · Health Defense Intervention
Information	1) By simulating the “clinical manifestations” of the human body after being infected with HIV, users can understand the disease manifestations after being infected with HIV. 2) Through the “knowledge corner” and “answer questions” during the battle, the information on AIDS-related knowledge is passed to the players.
Motivation	1) The goal of this game is to eliminate HIV, which can strengthen players’ motivation to eliminate the virus. 2) The “points ranking” in the game can stimulate players’ motivation to use this game. 3) “Knowledge corner” can help players acquire AIDS-related knowledge and further stimulate healthy players to have the motivation to prevent HIV infection.
Behavioral skills	1) The behavior training of using condoms, improving antiviral medicine use, avoiding alcohol and drugs has been added to strengthen the player’s refusal of dangerous sex, refusal of intravenous drug use, and obtain antiretroviral medicine for pre-exposure prophylaxis (PrEP)

## Methods/design

### Study design

Study participants will be recruited from adolescent volunteers and allocated to one of the four randomized groups after completing a baseline survey (Fig. 1) (AIDS Fighter · Health Defense intervention group 1; AIDS Fighter · Health Defense intervention group 2; control group 1; control group 2). Participants are required to complete the assessment four weeks later and three-month, six-month follow up visit after the intervention. Our hypotheses are:
There is no statistical difference between AIDS Fighter · Health Defense intervention group 1 and AIDS Fighter · Health Defense intervention group 2 in AIDS-related knowledge, stigma attitude, risk behaviors attitude and the incidence of risk behavior;Compared with adolescents in the control groups, those in the AIDS Fighter · Health Defense intervention groups will have More AIDS-related knowledge, less AIDS-related stigma and fewer AIDS-related risk behaviors.Comparison between control group 1 and control group 2, group 1 will show better effects in improving AIDS-related knowledge, attitude and behaviors.

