#### Game data management

Educational resources can be edited and upload to the “knowledge corner” through the management system, and the system can realize the following data collection functions:1) Player’s basic personal information; 2) Player’s points and rankings; 3) Player’s message and consultation information; 4) Player’s answers to questions; 5) When did the player log in to the game and how long has it been used; and 6) What did the players learn in the “knowledge corner”.

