### Intervention group: overview

#### AIDS fighter · health defense intervention group 1

Participants will receive the educational game “AIDS Fighter · Health Defense” and will be required to play the game and learn AIDS education essays or videos in the “knowledge corner” at least 5 days a week and 20 min a day. A data management system will be used to monitor the time participants played in the game, and whether they have learned the content in the “knowledge corner”. After four weeks of intervention, the effect of the intervention will be evaluated by using the same questionnaire as applied in the baseline survey.

Participants will be informed that they will be recognized and rewarded after completing daily game tasks and completing four-week follow-up assessments according to the points ranking. The top 20% will receive a “Gold Award” and 50 RMB in cash, the middle 30% will receive a “Silver award” and 50 RMB in cash, and the lowest 50% will receive a “Bronze award” and 20 RMB in cash.

#### AIDS fighter · health defense intervention group 2

Participants will receive “AIDS Fighter · Health Defense”, without limitation in time to play the game or learn the content of the “knowledge corner”, and there are no incentives as recognition or rewards. Participants play this game according to their preference. Four weeks later, the same questionnaires will be used to measure the effect of their use of the game.

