## Discussion

In developed countries, the focus of AIDS prevention education is on the sexual behavior of high-risk groups, but the focus of AIDS education in our study is on the AIDS-related knowledge of adolescents. The awareness rate of AIDS knowledge among the public in developed countries might be higher than China, and existing studies are mainly aimed at high-risk groups, such as men who have sex with men and adolescents who have sex without condoms [18, 19]. But in China, the awareness rate of AIDS among the public is low [20], especially adolescents in poor areas and western China [21, 22].

Adolescents are in the sexually active period are a high-risk group of HIV infection [23], the awareness rate of AIDS among them is low [24], and the HIV infection rate is high in China [25], AIDS preventive education for them is crucial. Therefore, the target of HIV prevention education in China should be the public, especially adolescents.

To meet the need of AIDS education of adolescents, the educational game “AIDS Fighter · Health Defense” was developed. As mentioned above, AIDS Fighter · Health Defense is a theory-based AIDS education game that can provide knowledge and skills to adolescents to prevent AIDS. Whether adolescents are interested in AIDS Fighter · Health Defense and insist on using it is the key to this study. If the game does not appeal to adolescents, it will not be popularized among them, nor have educational significance. To promote the use of this game by adolescents, the game is designed to be highly interactive and interesting, including gamification elements as levels, points, answering questions, rankings, and rewards. In the levels of the game, seven different organs and systems of the human body are simulated, it can vividly show the way HIV invades the human body and its performance if infected with HIV. This can not only improve the fun of the game, but also popularize the process of HIV invading the human body, which may increase users’ willingness to play the game and prevent AIDS.

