Four arms were designed in our research, including two intervention arms and two control arms. Participants in the two intervention groups will receive AIDS Fighter · Health Defense, one of which will strictly control the time spent in the game and provides incentives to increase motivation to use the game; Another group will receive AIDS Fighter · Health Defense, but without time limitation or incentives; One of the two control groups is classroom teaching and the other is autonomous learning. By comparing the intervention groups with the control groups, it can be found whether AIDS Fighter · Health Defense is better than classroom teaching and autonomous learning in improving participants’ AIDS prevention ability; By comparing the two intervention groups, we can figure out whether AIDS Fighter · Health Defense is attractive, whether players will voluntarily use the game to improve AIDS prevention capabilities. This will determine whether the game can be promoted on a large scale. By comparing the two control groups, we can understand the difference between classroom learning and autonomous learning in improving AIDS prevention capabilities. Such a design could see the differences in the effects of game-based intervention, classroom teaching, and independent learning in AIDS education. And provide evidence for choosing different AIDS education methods.

We hope that the game-based interventions can be widely used in AIDS education in China and other countries. However, some countries are exam-oriented in evaluating the effect of education and there may be some resistance to the promotion and application of the game; parents may worry that their children will be addicted to the game and affect their academic performance [26, 27]. To address this problem, we can perform identity authentication when the player enters the game and prevent minors from being addicted to the game by limiting the online time.

“AIDS Fighter · Health Defense” could be suitable for the public, high-risk groups of AIDS, and HIV-infected people. It could be an auxiliary educational tool for AIDS prevention for the public and high-risk groups, and for HIV-infected people to maintain long-term ART adherence and keep virus suppression. We believe that with the development of this study, we can provide an AIDS education method for China and other countries to improve the ability to prevent AIDS of public and the quality of life of HIV infected.

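### Hypothesis 1 predicts no difference between the two game arms, but with no margin and only difference tests a non-significant result could be taken as support for equality

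*Protocol article*

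**What the plan says.** The Study design section lists three hypotheses. The first is that "There is no statistical difference between" intervention group 1 and intervention group 2, and it covers four outcomes: "in AIDS-related knowledge, stigma attitude, risk behaviors attitude and the incidence of risk behavior".

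The two arms differ in how play is prompted (Intervention group: overview). Group 1 must play "at least 5 days a week and 20 min a day" and is rewarded according to points ranking. In group 2, "Participants play this game according to their preference", with no recognition or rewards.

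The Data management and statistical analysis section names ANOVA for the four-week scores, worded as intervention groups against control groups. It names repeated measures ANOVA across the four arms for behaviours at three and six months. Significance is P ≤ 0.05. The article states no equivalence or non-inferiority margin. The Recruitment section bases the sample size on power to detect changes: 131 per group for 80% power, 145 after 10% attrition, 580 in total.

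The Discussion says that comparing the two intervention groups will show whether the game is attractive and whether players will use it voluntarily, and adds: "This will determine whether the game can be promoted on a large scale".

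**The concern.** A difference test can give evidence against equality. Failure to reject is not evidence for it. Here the study's own prediction is the null hypothesis, so the less precise the trial, the more easily the prediction appears to be met: higher attrition or a noisier questionnaire would both help it.

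At stake is the claim that adolescents left to play as they like do as well as those who are required and paid to play. The Discussion links the prospects for wide promotion to that comparison. A non-significant result could be cited for promotion while the data remain compatible with a meaningful loss in group 2.

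A smaller, separable issue is that the comparison is also meant to show whether players use the game voluntarily, yet game use is not among the outcomes in the Outcomes and data collection section.

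**Working it through.** **Inputs from the article.** 131 evaluable per arm, 80% power, significance at P ≤ 0.05, 10% attrition, four equal arms.

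**Assumed, because the article does not say.** Two-sided test; one continuous outcome; pairwise comparison of group 1 with group 2; all gaps and margins in SD units.

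**The plan's own figure.** The 131 cannot be reproduced, as no effect size, SD or test is given. It can be solved backwards:

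- SE of a difference in means = √(2/131) = 0.1236 SD.
- Gap detectable with 80% power = (1.960 + 0.842) × 0.1236 = 0.346 SD.
- Attrition: 131/0.9 = 145.6 and 131 × 1.1 = 144.1, so 145 is consistent with 10%. 4 × 145 = 580.

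**Precision of the comparison.** 95% CI half-width = 1.96 × 0.1236 = 0.24 SD. This is also the gap at which the chance of a non-significant result is about one half.

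**Chance of a non-significant result by true gap d.** To a close approximation it is Φ(1.96 − d/0.1236). The table uses the noncentral t distribution with 260 degrees of freedom, which differs by less than half a percentage point.

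| True gap (SD) | d/SE | Chance non-significant |
|---|---|---|
| 0.10 | 0.81 | 87% |
| 0.20 | 1.62 | 64% |
| 0.25 | 2.02 | 48% |
| 0.30 | 2.43 | 32% |
| 0.346 | 2.80 | 20% |
| 0.40 | 3.24 | 10% |

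**What 131 per arm supports if the hypothesis is recast as non-inferiority.** Power = Φ(margin/0.1236 − 1.96), one-sided 2.5%, true difference zero. Evaluable n per arm for 80% power = 2 × ((1.960 + 0.842)/margin)².

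| Margin (SD) | Power with 131 per arm | n per arm for 80% power |
|---|---|---|
| 0.20 | 37% | 393 |
| 0.25 | 53% | 252 |
| 0.30 | 68% | 175 |
| 0.35 | 81% | 129 |
| 0.40 | 90% | 99 |

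Two-sided equivalence (two one-sided tests at 2.5% each) is more demanding: with 131 per arm, power is 36% at a 0.30 SD margin and 80% only at about 0.40 SD.

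**The case against.** Several stronger readings are tempting, and the article does not support them.

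- A reader might infer that a false finding of no difference is likely whenever a real gap exists. That holds only below about 0.24 SD. At 0.346 SD, the gap implied by the stated power, the chance is 20%.
- A reader might take the percentages as the chance that hypothesis 1 as written appears met. They are not, because it spans four outcomes. With a 0.20 SD gap on each of the three scores, the chance that all three are non-significant runs from 0.636³ = 26% if independent to 64% if perfectly correlated. At 0.30 SD it runs from 0.323³ = 3% to 32%. A four-arm omnibus F test can move the other way: if only groups 1 and 2 differ and the controls sit midway, it is non-significant 76% of the time at 0.20 SD.
- A reader might infer a fixed rule that hypothesis 1 is confirmed when an ANOVA gives P > 0.05. No such rule is written, and the four-week ANOVA is worded for game arms against control arms, so no test of group 1 against group 2 on the scores is specifically named.
- A reader might infer that voluntary use will be judged from questionnaire scores. The Discussion does not say which measure will be used, and the system records "When did the player log in to the game and how long has it been used".

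It is also fair that this is one of three hypotheses, that none is labelled primary, that the game-versus-control comparison is untouched, and that the promotion statement is a sentence in the Discussion and not a prespecified rule. A fuller protocol or analysis plan may exist.

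These points limit the size of the problem and leave the fault in place. The published hypothesis has a form that the named tests cannot support, and an unseen plan could repair it only by replacing the hypothesis.

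**Conclusion.** The point holds as a fault of inferential form. A no-difference hypothesis without a margin, alongside difference tests only, leaves room for non-significance to be taken as support for equality, on a comparison that the Discussion links to large-scale promotion. That non-significance would be read this way is an inference from the Study design and Discussion sections, though a fair one.

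The size depends on a gap that the article does not give. Under the stated assumptions, small gaps would more often than not be missed, while gaps near 0.35 SD or larger would usually be detected. The planned size can show non-inferiority with reasonable power only for a margin about as wide as the whole effect the trial can detect.

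The usage point is secondary. The Discussion says that whether adolescents "insist on using it is the key to this study", and use is already logged, yet it is not a listed outcome.

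**What to change.** Choose one of two routes.

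1. **Estimation only.** Report the group 1 minus group 2 difference with a 95% CI for each of the four outcomes, and state that no claim of equality will be drawn from non-significance. This costs only wording.
2. **Non-inferiority of group 2 to group 1.** Name the outcomes it covers, and say so openly if it is limited to the knowledge score. Justify a margin in score points for each and fix it before any outcome data are seen. Conclude non-inferiority only if the 95% CI excludes the margin; otherwise report 'not shown'. State that 131 per arm gives about 80% power only for margins of about 0.35 SD or wider (53% at 0.25 SD), so a tighter margin may not be demonstrable without more participants.

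Either way, name the analysis that compares group 1 with group 2.

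As a separate addition, make logged use over the four weeks (active days and minutes) a named outcome, described in group 2 and compared between groups 1 and 2. The data are already captured.

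The small downside is that the claim that voluntary play does as well as required play becomes harder to make.

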**Fig. 1 Fig1:**
[figure not shown]
Study workflow diagram

### Study participants

This study is aimed at improving the AIDS prevention capabilities of adolescent students. The inclusion criteria are: 1) Students aged 15–24 years; 2) Participants have clear consciousness, no mental disorders, and able to read and express themselves; 3) Participants were informed about the study and voluntarily participated in the study (< 16 years old requires the consent of the guardian). Those who are diagnosed as HIV positive will be excluded from the study.

### AIDS fighter · health defense: overview

#### Game design

Goal setting has been identified as an effective behavior change procedure [15]. The storyline of the game is that HIV launched an attack on the human body, and the goal is to control the hero to fight with HIV and eliminate it. During the battle, the hero must obtain antiretroviral medicine in the game and refuse the behaviors of condomless sex, drugs and alcohol.

Seven levels were contained in the game: immune system, blood system, skin and mucous membrane system, nervous system, respiratory system, digestive system, urogenital system. There will be corresponding animation prompts for the success or failure of the game. If they fail, it will prompt them that HIV has invaded the human body, and display pictures of symptoms corresponding to the level of content as a warning education. The game interface is shown in Fig. 2.

**Fig. 2 Fig2:**
[figure not shown]
Game design. (There are 6 interfaces in the picture. *Interface 1* is the login interface, including buttons of “start game”, “knowledge corner” and “point rankings”; *Interface 2* is the battle process of the game; *Interface 3* is a ranking of points; *Interface 4* is the “Challenge to answer quizzes”; *Interface 5* is the “knowledge corner”; *Interface 6* is the data management system)

#### Challenge to answer quizzes

Participants will have a chance to answer questions if they failed during the battle. If they answer correctly, they will be resurrected and continue to fight, otherwise, the game will fail. Questions include knowledge of AIDS prevention, antiretroviral treatment, pre-exposure and prophylaxis.

#### Knowledge corner

The “knowledge corner” contains a variety of AIDS knowledge, as AIDS prevention, diagnosis, antiretroviral treatment, pre-exposure prophylaxis, etc. What is taught in the form of texts, pictures and videos. Players can earn points by reading articles or watching videos, and the points are included in the rankings; Moreover, players can leave a message in the “Consultation” column, or conduct online consultation by identifying the QR code of the Internet hospital.

